### Recruitment

Patient recruitment will occur at Hamilton Health Sciences (i.e., Juravinski Hospital, Hamilton and Hamilton General Hospital), St. Joseph’s Healthcare Hamilton, and Kingston Health Sciences. All surgeons who perform elective non-bariatric surgery at these sites will be made aware of the study via workshops and internal communications. Patients will be identified by the surgeons, their administrative assistants, patient navigators, and/or study investigators at the time of referral or at the time of their initial preoperative consultation. Surgeons and/or other clinicians within a patient’s circle of care will introduce the study to participants at the time of their preoperative visits. Patients meeting inclusion criteria based on a review of their electronic medical record will be approached by designated research personnel at the time of their initial surgical consultation in clinic. If the patient is not identified in time, or if it is not feasible for the research personnel to approach the patient in person at the time of their consultation, the patient will be contacted by telephone within one-week of their consultation. At the time of initial contact between the study personnel and patient, the study will be introduced, and eligibility will be confirmed. Once eligibility is confirmed, the written informed consent process will ensue. After documentation of written informed consent, patients will be registered using a web-based randomization system. Consecutive patients will be allocated 1:1 according to a computer-generated randomization schedule to one of the two treatment arms. Randomization will be stratified by center and will employ randomly permutated blocks.

### Planned trial interventions

#### Intervention group (VLED protocol plus counseling)

All patients in the intervention group will receive patient counseling on weight loss and an active VLED protocol. The preoperative VLED protocol will utilize commercially available weight loss products, such as Optifast® 900, Medimeal®, or a similar product. Patients will receive a 3-week supply. They will start taking the VLED 3 weeks and 2 days prior to their surgery date (i.e., 23 days prior to their surgery date) and finish the intervention the evening of their second last day prior to surgery. This timeframe was chosen to not interfere with any other perioperative intervention required for a given surgery (e.g., bowel preparation, carbohydrate loading). They will be instructed to consume four packets daily. This provides a total energy intake of 900 kcal. Patients will also be able to consume up to 2 cups of low-calorie vegetables per day along with the meal replacement product. They will be provided with a handout containing specific instructions. Patients will keep self-report diaries of their dietary intake and activity levels. Patients enrolled in the trial and assigned to the VLED group who are diabetics will be referred to a diabetes educator nurse practitioner for management of their insulin dosing and/or other anti-hyperglycemic medications throughout the duration of the intervention period.

The current protocol in use at our local Bariatric Surgery Center utilizes four doses commercially available VLED daily and the duration varies between 1 and 3 weeks based on liver size and BMI. We have adapted this for the purposes of the present trial as presented in Additional file 1. To standardize the approach for non-bariatric surgery, we propose an intervention period of 3 weeks. In our systematic review of preoperative VLEDs prior to non-bariatric surgery, 95% CIs for weight loss resulting from programs lasting between 3 and 8 weeks overlapped significantly [24]. This plateau coupled with time constraints for the preoperative waiting period for certain patient populations (e.g., cancer patients), served as reasoning for our 3-week intervention period. Our systematic review identified protocols varying from 0.46 to 26 weeks that were safe and efficacious, and thus we are confident that our intervention period is appropriate [24]. In our systematic review and meta-analysis, Optifast® was the most commonly studied VLED liquid formulation (35.7% of included studies) and daily target caloric intake ranged from 450 to 1400 kcal per day [24].

Adherence to a preoperative 2-to-3-week regimen of preoperative VLED prior to bariatric surgery ranges from 80 to 90% [27, 28]. In our systematic review and meta-analysis evaluating the use of VLEDs in non-bariatric surgery, reported adherence ranged from 94 to 100% among the included studies, with much longer durations of intervention (0.46–24 weeks) [24]. We anticipate adherence in this study will be similar and range between 80 and 100%. To increase adherence with the study medication, we will cover the cost of the VLED and have patients complete a diet diary.

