**Methods:**

The proposed trial will be a multi-center, surgeon, outcome assessor, and data-analyst blinded, parallel pilot randomized controlled trial (RCT). Patients older than 18 years of age with a body mass index (BMI) of greater than 30 kg/m^2^ undergoing major elective non-bariatric surgery will be eligible for inclusion. Consecutive patients will be allocated 1:1 according to a computer-generated randomization schedule. Randomization will be stratified by center and will employ randomly permutated blocks. All patients in the intervention group will receive standard patient counseling on weight loss and an active VLED protocol. The preoperative VLED protocol will utilize commercially available weight loss products for three weeks preoperatively. The primary outcomes (randomization percentage, recruitment rate, intervention adherence, follow-up completion, network development) will assess feasibility. Descriptive statistics will be used to characterize the study sample.

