#### Feasibility outcomes

Randomization percentage: Defined as the number of patients agreeing to participate in the RCT and being randomized to treatment or control divided by the number of patients approached for participation in the RCT. A randomization percentage of 70% or greater will support the feasibility of a full RCT. A lesser randomization percentage may be feasible with modifications.Recruitment rate: Defined as the number of patients randomized into the RCT per month. We will aim for a rate of 16 patients per month (i.e., 4 patients at each of 4 sites per month). A recruitment rate of equal to or greater than this will support the feasibility of a full RCT. A lesser recruitment rate may be feasible with additional sites for the full RCT. At present, we anticipate participation of at least 10 sites in the definitive trial. If each site recruited at least 4 patients per month, this would equate to a minimum 48 patients per year at a given site. Thus, recruitment over 2.5 years would achieve our anticipated study sample size of approximately 1200.Intervention adherence: Defined as the number of preoperative VLED doses taken divided by the total number of doses prescribed for each participant randomized to the intervention arm. Adherence will be self-reported via written diaries. A mean adherence of greater than 80% (i.e., completing 80% or more of doses) will be our benchmark for feasibility in the present study. Adherence will also be measured through matching actual preoperative weight loss with expected preoperative weight loss. As per our systematic review evaluating preoperative VLEDs in patients undergoing bariatric surgery, patients receiving preoperative VLEDs for 2–3 weeks prior to bariatric surgery, they loss approximately 5% of their pre-VLED weight [18]. Therefore, a study participants expected weight loss will be defined as 5% of their pre-VLED in kilograms. We will subtract their expected weight loss from their actual weight loss as a measure of adherence.Follow-up completion: Defined as completion of the pre-VLED, post-VLED, and 30-day postoperative visits, along with complete anthropometric measures and study questionnaires. A follow-up completion rate of greater than 90% will support the feasibility of a full RCT.Network development: Defined as recruiting from all four participating centers at the aforementioned rate. Additionally, we will aim to extend our multi-disciplinary network to at least 10 centers throughout the course of this pilot RCT in preparation for the full RCT.Other findings: Unexpected and/or findings unique to this pilot trial will be reported narratively.

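### The stated start and stop days of the VLED span 22 dosing days (up to 88 packets), but the supply and intervention period are three weeks (84 packets)

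*Protocol article*

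**What the plan says.** The dosing schedule is in the Protocol article, under Intervention group (VLED protocol plus counseling). One paragraph fixes four things:

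- Supply: "Patients will receive a 3-week supply".
- Start: "They will start taking the VLED 3 weeks and 2 days prior to their surgery date", which the article itself restates as 23 days.
- Stop: participants "finish the intervention the evening of their second last day prior to surgery".
- Daily dose: "They will be instructed to consume four packets daily".

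The three-week length is repeated elsewhere. The abstract's Methods paragraph speaks of "commercially available weight loss products for three weeks preoperatively", and the rationale later in the intervention section says "we propose an intervention period of 3 weeks".

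The dose count feeds a primary feasibility outcome. Under Feasibility outcomes, adherence is the "number of preoperative VLED doses taken divided by the total number of doses prescribed for each participant" in the intervention arm, and the benchmark is "A mean adherence of greater than 80" percent.

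**The concern.** The start day, stop day, daily dose and supply cannot all hold together. The stated dates cover one calendar day more than three weeks, so a participant who follows the dates at four packets a day runs short. The likely origin is subtracting 2 from 23 to get 21, which counts only one of the two end days.

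The direct problem is practical: the written schedule asks for more product than is handed out. There is also a smaller issue in the adherence outcome. The supply and the three-week period point to 84 doses prescribed, while someone counting the stated calendar days would arrive at as many as 88. If sites or analysts differ on this, identical diaries would be scored differently.

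**Working it through.** **Inputs**, all from the intervention-group section: start on day −23; stop on the evening of day −2 (surgery is day 0, the last day before it is −1, the second last is −2); four packets daily; three-week supply. The article prints no packet count, so 84 and 88 below are derived.

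**The plan's own figure.** Three weeks = 21 days, and 21 × 4 = 84 packets. From the dates, 21 comes out only as elapsed days: 23 − 2 = 21.

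**Dosing days on the stated dates.** Counting both end days: (−2) − (−23) + 1 = 22 days, and 22 × 4 = 88 packets. Excess over supply: 88 − 84 = 4.

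**When the supply runs out.** With four packets daily from day −23, 84 / 4 = 21 days, and the last covered day is −23 + 21 − 1 = −3. Day −2 has no product.

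**Allowing for a partial first day.** Days −22 to −2 are (−2) − (−22) + 1 = 21 days, which already use 21 × 4 = 84 packets. With k packets on day −23 the total is 84 + k:

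| Packets on day −23 | Total needed | Excess over 84 | Score of a participant who takes all 84, if the total is the denominator |
|---|---|---|---|
| 0 | 84 | 0 | 100% |
| 1 | 85 | 1 | 84/85 = 98.8% |
| 2 | 86 | 2 | 84/86 = 97.7% |
| 3 | 87 | 3 | 84/87 = 96.6% |
| 4 | 88 | 4 | 84/88 = 95.5% |

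The figures agree only if no packet is taken on day −23, or if day −2 is shortened by the number taken on day −23.

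**Effect on the benchmark.** A mean of m on the 84 base becomes m × 84/88 on the 88 base. This is at or below 80% when m ≤ 80% × 88/84 = 83.8%. With a denominator of 85 the limit is 80% × 85/84 = 81.0%. The reading could therefore change only for a mean above 80% and up to 83.8% (or 81.0%) on the 84 base.

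Table 1 is not used as evidence for 22 full days. Its columns share boundary days, and it places randomization on day −23, so four packets on that day are not assured.

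**The case against.** The best defence is that the intended duration is plain. Three weeks is stated several times, and three weeks and two days less a two-day gap is 21 elapsed days. Randomization falls on day −23 in Table 1, so a full first day is doubtful. First-dose timing may be set in Additional file 1 or in the patient handout, neither of which is shown. The adherence denominator is defined by doses prescribed, not by calendar days, and nothing in the article proposes 88. Finally, stopping on day −3 or supplying four more packets would also resolve the mismatch, so the text does not dictate one remedy.

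Much of this stands. The intended length is three weeks, the first day may be partial, the unseen files may settle the start, and the adherence effect is hypothetical and small. What does not stand is the claim that the printed figures agree. The text has participants begin taking the product on day −23. Elapsed counting needs either no packet that day, which contradicts starting then, or a split of packets between the first and last days, for which the article gives no start time. This is a conflict between stated figures, not a detail left to a fuller document, and an unseen file cannot make those figures agree.

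**Conclusion.** The schedule is wrong as written, and the error is minor. The stated dates exceed the stated supply by 1 to 4 packets, at most one day's dosing. If calendar days were used as the denominator, measured adherence would fall by at most 4.5 points (100% to 95.5%), and the 80% benchmark would read differently only in the narrow band worked out above.

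This assumes that surgery is day 0, that some product is taken on day −23 as the text says, that every later day through day −2 carries four packets, and that a three-week supply means 21 days at that dose. Recruitment, follow-up and the sample size are unaffected.

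**What to change.** Start the VLED on day −22 (22 days before surgery) and keep the finish on the evening of day −2. That gives 21 days and 21 × 4 = 84 packets. It preserves the supply, the three-week period, the stop day and the diet-free day before surgery, and it puts the first dose after the day −23 randomization in Table 1. State that the adherence denominator is 84 doses prescribed per participant.

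Moving the stop to day −3 would also give 84 packets, but it changes the stated stop and leaves dosing to begin on the day of randomization. Issuing 88 packets would keep both dates but depart from the three-week period.

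The cost is a minor amendment. Under Protocol amendments, it goes to the ethics board before implementation and is then uploaded to the registration page. The intervention text and the Table 1 intervention window need editing, as do the handout and diary where they do not already match. No extra product is needed.

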#### Control group (counseling alone)

The control group patients will receive the pre-existing standard of preoperative care, which may include counseling for weight loss without prescription of a specific preoperative weight loss intervention, as this is meant to be a pragmatic trial. Currently, there are no standardized interventions aimed at optimizing obese patients prior to undergoing non-bariatric surgery. Briefly, counseling may consist of the surgeon, at the time of the preoperative clinic visit, discussing weight loss strategies such as decreased caloric intake and increased physical activity. Patients will not receive prescriptions for preoperative VLEDs, any other weight loss supplement, or any physical activity intervention aimed at promoting weight loss prior to surgery. Patients will keep self-report diaries of their dietary intake and activity levels.

#### Perioperative care for all study participants

Given the pragmatic nature of this trial, all patients will receive surgical care as per their respective surgeons. Dosing of preoperative antibiotics and venous thromboembolism prophylaxis will be performed for all included patients where appropriate. Intraoperative care and procedures, including anesthesia, will be determined as per the independent practitioners and the type of surgery. Patients will be enrolled in ERAS programs for postoperative recovery where appropriate.

### Outcomes

Detailed criteria for event adjudication are reported in Additional file 2. A blinded outcome adjudication committee will independently identify and report outcomes. This committee will be blinded to treatment allocation. Given that this is a pilot trial, the primary outcome will be feasibility.

#### Feasibility outcomes

Randomization percentage: Defined as the number of patients agreeing to participate in the RCT and being randomized to treatment or control divided by the number of patients approached for participation in the RCT. A randomization percentage of 70% or greater will support the feasibility of a full RCT. A lesser randomization percentage may be feasible with modifications.Recruitment rate: Defined as the number of patients randomized into the RCT per month. We will aim for a rate of 16 patients per month (i.e., 4 patients at each of 4 sites per month). A recruitment rate of equal to or greater than this will support the feasibility of a full RCT. A lesser recruitment rate may be feasible with additional sites for the full RCT. At present, we anticipate participation of at least 10 sites in the definitive trial. If each site recruited at least 4 patients per month, this would equate to a minimum 48 patients per year at a given site. Thus, recruitment over 2.5 years would achieve our anticipated study sample size of approximately 1200.Intervention adherence: Defined as the number of preoperative VLED doses taken divided by the total number of doses prescribed for each participant randomized to the intervention arm. Adherence will be self-reported via written diaries. A mean adherence of greater than 80% (i.e., completing 80% or more of doses) will be our benchmark for feasibility in the present study. Adherence will also be measured through matching actual preoperative weight loss with expected preoperative weight loss. As per our systematic review evaluating preoperative VLEDs in patients undergoing bariatric surgery, patients receiving preoperative VLEDs for 2–3 weeks prior to bariatric surgery, they loss approximately 5% of their pre-VLED weight [18]. Therefore, a study participants expected weight loss will be defined as 5% of their pre-VLED in kilograms. We will subtract their expected weight loss from their actual weight loss as a measure of adherence.Follow-up completion: Defined as completion of the pre-VLED, post-VLED, and 30-day postoperative visits, along with complete anthropometric measures and study questionnaires. A follow-up completion rate of greater than 90% will support the feasibility of a full RCT.Network development: Defined as recruiting from all four participating centers at the aforementioned rate. Additionally, we will aim to extend our multi-disciplinary network to at least 10 centers throughout the course of this pilot RCT in preparation for the full RCT.Other findings: Unexpected and/or findings unique to this pilot trial will be reported narratively.

#### Safety outcomes

The primary safety outcome will be all adverse events deemed secondary to the preoperative VLED. The adverse events will be recorded as dichotomous outcomes and described as either minor or serious, similarly to the OPTIWIN study: the largest medical weight loss RCT evaluating VLEDs (*n* = 273) [29]. Standardized definitions for adverse events are described in Additional file 3 (adjudicated outcome).

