## Materials and methods

### Pilot trial objectives

The objective of this pilot RCT is to determine the feasibility of a multicenter RCT comparing patients with obesity (i.e., BMI > 30 kg/m^2^) receiving VLEDs versus control prior to elective non-bariatric surgery in terms of perioperative outcomes. The specific feasibility objectives of this trial are as follows: (1) determine the feasibility of recruiting patients in a timely manner across local and outside sites; (2) determine adherence with preoperative VLEDs in patients with obesity undergoing elective non-bariatric surgery; (3) determine the feasibility of completion of follow-up; (4) determine our ability to develop a network of participating sites in a multi-site initiative; (5) determine the safety of administering preoperative VLEDs to patients with obesity undergoing elective non-bariatric surgery. We postulate this pilot RCT will demonstrate feasibility and thus offer support for a full RCT aimed at evaluating the efficacy of preoperative VLEDs in patients undergoing major non-bariatric surgery in terms of perioperative outcomes.

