#### Post-VLED completion

Patient-reported compliance will be assessed via a patient-completed diet diary that they will complete daily during the 3-week period prior to surgery. Both the treatment and control arms will complete these forms and give them to the research assistant in an opaque envelope on the date of their surgery. Patients in the control arms will be instructed to leave the VLED component of the form blank. Anthropometric measures will take place through a blinded research assistant. VLED-related safety data will be ascertained via a combination of patient self-reporting and EMR data. Paper questionnaires will be used to assess the presence of adverse events. QoL data will be ascertained via administration of an SF-36 questionnaire. Intraoperative difficulty will be assess using a short survey immediately following completion of the operation.

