### Analysis strategy

Descriptive statistics will be used to characterize the study sample. The outcomes of the pilot study will be descriptive in nature and will focus on feasibility. Differences in binary outcomes will be presented using absolute differences and corresponding 95% CIs. Similarly, differences in continuous outcomes will be presented as mean differences with 95% CIs. We will not conduct hypothesis testing for outcomes [36]. We will calculate aggregated measures for 30-day postoperative morbidity to compare this to the power calculation for the full RCT, to ensure an accurate power calculation is performed for the full RCT. There will not be a planned interim analysis in the present study. There are no subgroup analyses planned [37].

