#### Central outcomes adjudication committee (CAC)

Our CAC will be formed with the guidance of our expert co-investigators Drs. [name] and [name]. The CAC will be blinded and oversee data collection and event adjudication.

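### The primary safety outcome requires a blinded committee to attribute events to the diet, and no all-cause adverse event comparison covers the preoperative diet period

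*Protocol article*

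**What the plan says.** Under Pilot trial objectives, the fifth objective is to "determine the safety of administering preoperative VLEDs to patients with obesity undergoing elective non-bariatric surgery". The Safety outcomes section then defines the measure: "The primary safety outcome will be all adverse events deemed secondary to the preoperative VLED". On scale it says: "The adverse events will be recorded as dichotomous outcomes and described as either minor or serious". It marks the outcome as adjudicated and places the event definitions in Additional file 3, which is not part of the document at hand.

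The Outcomes section says of the adjudicators: "This committee will be blinded to treatment allocation". The section on the central outcomes adjudication committee repeats this: "The CAC will be blinded and oversee data collection and event adjudication".

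On collection, the Post-VLED completion section says: "Paper questionnaires will be used to assess the presence of adverse events". It adds patient self-report and record review, and describes the data as related to the VLED. The adverse event row in Table 1 is likewise limited to intervention-associated events, from day −23 to day +30.

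On analysis, the Analysis strategy section says: "Differences in binary outcomes will be presented using absolute differences and corresponding 95% CIs". No hypothesis tests are planned.

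**The concern.** Causation by the VLED is part of the outcome definition. To judge that an event was caused by the VLED, one would normally need to know that the VLED was taken, and the committee is denied that knowledge. The article does not say how the committee attributes an event, or whether an event in a control participant can qualify. Control participants are prescribed no VLED, so on the plain wording they can hardly have the outcome. Yet the analysis rule calls for a difference between arms.

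What the reported difference means therefore depends on a reading that the article does not settle, and the two readings err in different ways. Safety is a stated objective, and the Discussion says that the safety results will inform the full trial. Symptoms such as nausea, constipation or dizziness also occur in people who are not on a diet. A concurrent randomised control arm can separate that background from the effect of the diet, but only if events in both arms are counted by the same rule.

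**Working it through.** **The plan's own figure.** The only precision figure in the article is for follow-up completion: 82–95% at 90% with 88 patients. The Wilson interval has centre (p + z²/2n)/(1 + z²/n) and half-width z√(p(1−p)/n + z²/4n²)/(1 + z²/n). With p = 0.90, n = 88 and z = 1.96, the centre is 0.9218/1.0437 = 0.883 and the half-width is 0.0664/1.0437 = 0.064. The interval is 82.0–94.7%, which reproduces the stated figure. No figure is given for the safety outcome.

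**Inputs from the article.** 88 patients at 1:1 gives 44 per arm. The Introduction reports adverse event rates below 14% in most earlier studies. I use 14 points only as an illustrative true excess.

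**Assumptions not in the article.**
- b: background risk of an adverse event before surgery, 5–20%.
- e: true excess due to the VLED, 0 or 14 points.
- q: probability that a background event is deemed due to the VLED, 0.2–0.8.
- s: probability that a true VLED event is deemed due to the VLED, 0.6–0.9.

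**Expected between-arm difference.**
1. All events counted in both arms: (b + e) − b = e. The 95% CI is e ± 1.96√[(b+e)(1−b−e)/44 + b(1−b)/44].
2. Attribution blinded, same rule in both arms: (qb + se) − qb = se.
3. Exposure known or inferred, so no control event qualifies: (qb + se) − 0 = qb + se.

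Results in percentage points:

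| b | e | 1. All-cause (95% CI) | 2. Blinded, symmetric | 3. Control zero by construction |
|---|---|---|---|---|
| 5% | 0 | 0 (−9.1 to 9.1) | 0 | 1 to 4 |
| 10% | 0 | 0 (−12.5 to 12.5) | 0 | 2 to 8 |
| 20% | 0 | 0 (−16.7 to 16.7) | 0 | 4 to 16 |
| 5% | 14 | 14 (0.7 to 27.3) | 8.4 to 12.6 | 9.4 to 16.6 |
| 10% | 14 | 14 (−1.4 to 29.4) | 8.4 to 12.6 | 10.4 to 20.6 |
| 20% | 14 | 14 (−4.3 to 32.3) | 8.4 to 12.6 | 12.4 to 28.6 |

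Reading 2 is right when there is no effect and too small otherwise, by 14 − 12.6 = 1.4 to 14 − 8.4 = 5.6 points. Reading 3 shows harm even when there is none. Its result is really a single-arm rate: for instance, 6 attributed cases among 44 is 13.6% (Wilson 95% CI 6.4–26.7%), with no comparator behind it.

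**Which periods have an attribution-free outcome.** Under Clinical outcomes, overall 30-day morbidity is counted from the index operation, is adjudicated, and does not depend on cause. Mortality and intraoperative complications are also recorded. None of these covers the period from day −23 to surgery, which is when the diet is taken. The article names no all-cause adverse event outcome by arm for that window.

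**The case against.** Four points can be made in the plan's favour.

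- **Blinded attribution is not invalid.** If the blind holds and one rule is applied to everyone, control events judged compatible with a VLED effect are the background rate that the comparison subtracts. This stands. A reader might infer that the outcome can give no valid between-arm estimate at all; the article does not support that, because under this reading the estimate is diluted, not meaningless. Nor does it support a claim that the plan will show a large spurious harm: that needs allocation to be known or inferred, and the article says the committee is blinded.
- **Additional file 3 may settle the matter.** It may list event types that apply equally to both arms or say how relatedness is judged. This limits how firmly one can speak. It would not remove the attribution condition, which is in the outcome as stated.
- **The control arm is not wasted.** Postoperative harm is compared without attribution, and the SF-36 is collected in both arms after the diet. This stands, and it confines the gap to preoperative events. A quality-of-life score does not replace a count of those events.
- **The stakes are modest.** Feasibility is primary, the safety objective names no between-arm contrast, and no safety threshold or test is set. With 44 per arm, sampling error is also as large as most of the distortions shown above. This lowers the priority. It does not make the definition consistent.

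**Conclusion.** The statements on the outcome definition, the blinding of adjudicators and the reporting of differences must be reconciled. As written, either the control rate is zero by construction, or events in people prescribed no VLED are labelled as caused by it. Under the assumptions above, the first reading gives 1–16 points of apparent harm with no true excess. The second gives 8.4–12.6 points when the truth is 14, which errs towards missing harm. The direction of these effects follows from the definitions; their size rests on assumed values of b, q, s and e and is only illustrative.

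The gap is limited to the preoperative diet period. The point does not extend to postoperative harm, and it does not mean that blinding the adjudicators is itself a mistake. I rate it as a correction worth making, below the level of a critical fault.

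**What to change.** - Define the primary safety outcome as the proportion of participants with any adverse event (minor; serious), regardless of attribution, from randomisation to surgery. Collect it in both arms with the same questionnaire and record review, and report the absolute difference with its 95% CI.
- Leave events from surgery to day 30 to the existing morbidity outcome. A single all-cause count through day 30 would largely duplicate that outcome and let surgical complications swamp events related to the diet.
- Keep events attributed to the VLED as a descriptive listing in the VLED arm. State who judges causality and with what knowledge of allocation.
- Relabel the adverse event row in Table 1 to match, and word the questionnaire so that it can be given unchanged to control participants.

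The cost is a protocol amendment to the outcome wording, a higher raw event count and some extra event coding in the control arm. The questionnaire and record review already exist. One limit remains: participants are not among those listed as blinded, so self-reported symptoms may differ between arms for that reason alone. Using the same instrument in both arms reduces this but does not remove it.
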